### Randomisation, blinding and allocation concealment

Consented participants will be randomised (1:1) to the group exercise and behaviour-change intervention (intervention group) or group exercise alone intervention (control group) using the centralised computer randomisation service RRAMP (https://rramp.octru.ox.ac.uk) provided by the Oxford Clinical Trials Research Unit (OCTRU). This will either be undertaken directly by the site’s research facilitator or by contacting the trial office over the telephone, who will access the system on their behalf. Randomisation will be undertaken using a minimisation algorithm to ensure balanced allocation of participants across the two treatment groups, stratified by:

Hospital site.Type of joint replacement (THR or TKR).CCI of 1 to 3 versus ≥4.^20 21^

The minimisation algorithm will be seeded using simple randomisation and will have a probabilistic element introduced to ensure unpredictability of treatment assignment.

Baseline data will be collected during the preoperative assessment appointment and prior to randomisation. Therefore, the central randomisation system will issue a screening identifier (ID). Once the participant has been randomised, the central randomisation system will provide a participant ID to be used on all subsequent data collection forms. Sites will be responsible for linking the screening ID to the participant ID, with all linking information remaining at sites. This will be double-checked across the CRFs to ensure that the correct paperwork has been provided to the correct participant.

Due to the nature of the intervention, participants and those delivering the rehabilitation will be aware of the treatment allocation. By virtue of this design, it is not possible to blind participants, physiotherapists or the site researchers.

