#### Primary outcome

UCLA Activity Scale:^25^ This is a reliable and valid self-reported tool to assess physical activity.^33 34^ It assesses global activity levels with a grading system of 1 out of 10 points where one equates to ‘wholly inactive, dependent on others and cannot leave residence’ and 10 refers to ‘regularly participants in impact sports’.^25^

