#### Statistical analysis

A detailed statistical analysis plan (SAP) will be drafted early in the trial and will be finalised prior to any primary outcome analysis. This will be reviewed and will receive input from the Trial Steering Committee (TSC) and the DSMC.

All analyses will be undertaken on the intent-to-treat population, that is, patients will be analysed as they were randomised regardless of the treatment received. Sensitivity analyses will be undertaken on the per-protocol population to assess a range of potential biasses that could have resulted from loss to follow-up, protocol deviations and withdrawal (including mortality). Numerical and graphical summaries of all data will be presented including descriptions of missing data at each level.

Estimates of treatment effects will be reported with 95% CIs. The primary outcome measure, UCLA Activity Scale at 12 months post-randomisation, will be analysed using a mixed effects linear regression model adjusted for baseline activity, 6 month time point and the stratification factors. Centre will be included as a random-effect to take account of their potential heterogeneity and type of operation, comorbidity index and other time points (baseline and 6 months) will be included as fixed-effects. Treatment by 6 month time point interaction will also be included in the model to allow time specific treatment effects to be calculated The adjusted difference in the means with corresponding 95% CI will be reported together with the mean and 95% CIs for each treatment group. If not normally distributed, then transformation to normality will be considered. If this is not possible, non-parametric techniques (for example Mann-Whitney or Kruskal-Wallis test) will be used with no adjustment. Consistency of any observed intervention effect will be explored using forest plots for various subgroups including site, type of operation (TKR and THR) and comorbidity index using interactions. No formal testing of interaction effects will be undertaken as the trial is not powered to detect these and the effect of the intervention is expected to be similar in the THR and TKR subgroups, although their baseline physical activity may be different, which will be taken into account in the analysis.

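### If UCLA scores are judged non-normal, the primary analysis can fall back to an unadjusted rank test, which contradicts the promised adjusted mean difference and is not needed at this sample size

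*Protocol article*

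**What the plan says.** All of this is in the protocol article.

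- **Outcome (Primary outcome).** "It assesses global activity levels with a grading system of 1 out of 10 points", so the score is a ten-level integer.
- **Planned model (Statistical analysis).** A "mixed effects linear regression model adjusted for baseline activity, 6 month time point and the stratification factors", with centre as a random effect.
- **Planned result (same section).** "Estimates of treatment effects will be reported with 95% CIs", and for the primary outcome specifically, "The adjusted difference in the means with corresponding 95% CI will be reported".
- **Baseline (same section).** Of hip and knee patients it says that "their baseline physical activity may be different, which will be taken into account in the analysis".
- **Distribution rule (same section).** "If not normally distributed, then transformation to normality will be considered. If this is not possible", then "non-parametric techniques (for example Mann-Whitney or Kruskal-Wallis test) will be used with no adjustment".
- **Allocation (Randomisation, blinding and allocation concealment).** "Randomisation will be undertaken using a minimisation algorithm to ensure balanced allocation of participants across the two treatment groups"; the factors are hospital site, hip or knee, and comorbidity index 1 to 3 versus 4 or more.
- **Sample size.** A difference of 1 point with SD 2.5 (standardised 0.4), 80% power, 5% two-sided, 20% loss. The total was 250 and is now 260, with about 1.5:1 expected at the end.

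**The concern.** The section sets a target for the primary outcome and then a rule that cannot reach it. An unadjusted rank test has no place for baseline activity, the 6-month score, centre, operation type or comorbidity index. Allocation was minimised on the last three, which is itself a reason to keep them in the analysis. The rule also names no effect measure. The trial was sized on 1 UCLA point and cites a minimally important within-person change of 0.92 points, so a reader will want the answer in points. Transformation, the intermediate step, would also take the result off that scale.

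The trigger is loose. The text does not say whether scores or residuals are to be judged, or by what standard, so the choice of primary test would be settled after the outcome data have been looked at. This is not a detail left to the statistical analysis plan: the protocol itself fixes the absence of adjustment. Because continuous secondary outcomes are to be analysed by similar methods, the rule may carry over to them.

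**Working it through.** **1. The plan's own figure.** Per arm at 1:1: n = 2 × (1.960 + 0.842)² × (2.5/1)² = 2 × 7.85 × 6.25 = 98.1, so 99. Total 198/0.8 = 247.5. The t-test version gives 100 per arm, and 200/0.8 = 250, as stated. At 1.5:1 the normal formula gives 82 + 123 = 205, and 205/0.8 = 256 (t-test version 258), close to 260. The sample size therefore reproduces as an unadjusted comparison.

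**2. Evaluable numbers.** 260 × 0.8 = 208; at 1.5:1, 124.8 versus 83.2.

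**3. Power by formula, near-normal outcome.** SE = 2.5 × √(1/124.8 + 1/83.2) = 0.354, and 1/0.354 = 2.826.

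- Unadjusted comparison of means: Φ(2.826 − 1.960) = 81%.
- Mann-Whitney: multiply 2.826 by the square root of its asymptotic relative efficiency. At 0.955 (normal data), Φ(2.762 − 1.960) = 79%. At the lower bound of 0.864, Φ(2.627 − 1.960) = 75%.
- Baseline-adjusted model: divide 2.826 by √(1 − ρ²). The baseline-to-12-month correlation ρ is not in the document, so it is assumed over a range:

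| ρ (assumed) | Adjusted model | Minus Mann-Whitney (79%) |
|---|---|---|
| 0.3 | 84% | 5 points |
| 0.4 | 87% | 8 points |
| 0.5 | 90% | 11 points |
| 0.6 | 94% | 15 points |

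**4. Simulation on integer 1-10 scores.** 125 versus 83 evaluable, true shift 1 before rounding and clipping, 2000 trials per setting. The linear model was adjusted for baseline only, with ordinary standard errors.

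| Scores | ρ | Mann-Whitney power | Adjusted power | Adjusted type I error |
|---|---|---|---|---|
| Near-normal | 0.3 | 78% | 83% | 4.0% |
| Near-normal | 0.5 | 78% | 88% | 5.3% |
| Near-normal | 0.6 | 79% | 93% | 4.6% |
| Right-skewed | 0.3 | 91% | 89% | 4.8% |
| Right-skewed | 0.5 | 91% | 93% | 5.0% |
| Right-skewed | 0.6 | 91% | 96% | 5.1% |

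The skewed scores had a smaller SD (about 2.2, against 2.3 for the near-normal ones), so methods should be compared within a row and not across the two kinds of score.

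A separate simulation of the same size with robust standard errors gave type I error of 4-6%, including for skewed scores. For near-normal scores, Mann-Whitney had 77-78% power against 82%, 89% and 91% for the adjusted model at ρ of 0.3, 0.5 and 0.6. For skewed scores, Mann-Whitney had about 90% against 87-96%, that is, from about 3 points better to about 6 points worse.

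**5. Why the missing criterion matters.** In simulated trials of near-normal integer scores (129 versus 79), a Shapiro-Wilk test rejected normality of the raw scores in 100% of trials. On model residuals it rejected in 10-35% with the design effect present, and in up to 50% under the null. The protocol names no test; this shows only that the unstated choice between scores and residuals can decide the primary analysis.

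**The case against.** Several points on the other side are sound.

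- **The fallback may rarely operate.** A reader might infer that it is bound to operate, because integer scores can never be exactly normal. The document does not support that. It names no normality test, residuals are the usual object of the check, and transformation must fail first. Read literally on raw scores, the rule would mean the planned linear model could never be used, which is hardly the intention.
- **The rank test does not always lose power.** The larger losses belong to near-normal scores, where the fallback is least likely to be invoked. With clear skew, the rank test can be slightly better than the adjusted model if the baseline correlation is low.
- **Design power is almost intact.** The sample size assumed no adjustment, and Mann-Whitney gives about 79% against the planned 80%. The larger gap is power above plan, and it rests on a correlation that the document does not give.
- **The check need not be unblinded.** A reader might infer that the test would be chosen with allocation known. The text does not say so; a pooled, blinded look at the distribution is compatible with it, and the analysis plan is to be final before any primary outcome analysis.
- **Some estimate could still be given.** The general commitment to report effects with 95% CIs is unconditional, and an unadjusted Hodges-Lehmann shift could accompany the test.

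All five stand as limits on the size of the point. None removes the contradiction: no estimate is named for the fallback, an unadjusted shift is not the promised adjusted mean difference, and the text rules out adjustment outright.

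**Conclusion.** The point holds as an internal contradiction and a poor stated rule for the primary outcome. Loss of the adjusted estimate and of the adjustment follows from the text alone and needs no assumption about power. The choice of test depends on the outcome data without a criterion, even if the check is blinded. The fallback is possible because a 1-10 integer score cannot be made exactly normal; its probability cannot be stated from the document.

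Non-normality alone does not justify leaving the adjusted model, given type I error near 5% at about 208 evaluable. The power consequence is secondary and goes in both directions according to the shape of the scores. These figures rest on assumed correlations of 0.3 to 0.6, on 20% loss and 1.5:1 allocation as stated, and on a simplified model without centre effects or 6-month data.

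**What to change.** For the primary outcome, delete both the transformation step and the unadjusted rank-test fallback. State that the adjusted mixed model is the primary analysis whatever the distribution of UCLA. If residuals look poor, report robust or bootstrap CIs for the same 12-month adjusted mean difference. An adjusted ordinal model (for example proportional odds with the same covariates) or a rank test may be added as a pre-specified sensitivity analysis. State whether the same rule applies to the continuous secondary outcomes.

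The cost is a change of wording in the protocol and the analysis plan, and one extra analysis. No new data are needed. The downside is a possible small loss of power against a rank test if scores are strongly skewed and the baseline correlation is low.

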#### Health economics

Respecting an *efficient trial design*, only if the data indicates clinical effectiveness of the experimental intervention (for the UCLA Activity Scale and LEFS), will additional funding be sought to analyse the health economic and utilisation data, to determine the cost-effectiveness of the intervention.

#### Data management

All data will be processed according to the Data Protection Act 2018.^44^ All documents will be stored safely in confidential conditions. Trial-specific documents, except for the signed consent form and follow-up contact details, will refer to the participant with a unique study participant number, not by name. Participant identifiable data will be stored separately from trial data. All trial data will be stored securely in offices or online in secure trial databases, only accessible by the central trial team in Oxford and authorised personnel.

### Trial status

The trial is funded for 36 months and commenced in August 2018. Recruitment is expected to be complete by April 2020 with the final follow-up visit for the final participant completed by April 2021. The trial will be completed by August 2021.

### Patient and public involvement

Patient involvement began during protocol development and continues throughout the trial. A patient-member will attend all TSC meetings. The same patient-member is a co-investigator, providing insights into the trial conduct, particularly on data collection processes, and will help interpret the findings to inform on the implications of the research during the trial’s dissemination phase.

## Ethics and dissemination

Ethical approval was gained from the South Central (Oxford B) Research Ethics Committee (Approval Date: 23 October 2018; Reference Number: 18/SC/0423). The trial was prospectively registered. A DSMC and TSC was appointed to independently review the data on safety, protocol adherence and recruitment to the trial. Direct access will be granted to authorised representatives from the sponsor and host institution for monitoring and/or audit of the trial to ensure compliance with regulations. Anonymised data will be shared outside the research team when required. Researchers outside the trial team may formally request for a specific data set using a data request form, which will be part of the Data Management Plan. All such requests will need to be approved by the TMG.

Reporting of the trial will be consistent with the CONSORT 2010 Statement (patient reported outcomes and non-pharmcological interventions)^45^ and Template for Intervention Description and Replication (TIDieR)^46^ guidelines. A summary of the results and trial materials will be made available via the trial website on completion of the trial. We will submit the final report to a peer-reviewed academic journal.

## Discussion

This paper presents the research protocol for the PEP-TALK trial. Following a THR and TKR, only 50% of people reach WHO recommended levels of physical activity.^15 47 48^ Those who are least likely to meet these levels are people with a higher body mass index and with comorbidities.^49^ These patients have the most to gain from being more physically active. If this trial’s experimental intervention is shown to be effective, this intervention could have a significant and sustained impact on improving the management of comorbidities such as diabetes, cardiovascular diseases, depression and hypertension for over 103 000 people annually in England and Wales.^1^ It is proposed that, in such an instance, this should be considered for implementation in healthcare services. This could help address the global challenge which multi-morbidities and an ageing population are expected to have on health and social care services.
